## Abstract

**Background:**

Chronic Pain (CP) affects approximately one in five adults and is associated with emotional distress, disability, reduced productivity and substantial healthcare and societal costs. Acceptance and Commitment Therapy (ACT) has demonstrated effectiveness in improving emotional, behavioral and functional outcomes in individuals with CP, but access to ACT is frequently limited by geographic, organizational and workforce barriers. Internet-based interventions may help overcome these limitations by increasing accessibility, reducing treatment costs and improving scalability.

**Objective:**

This study evaluates the effectiveness and cost-effectiveness of MobACT, a guided internet-based ACT programme for Italian adults with CP. The primary effectiveness endpoint is the post-intervention assessment (T1).

**Methods and analysis:**

This two-arm randomized controlled trial will allocate adults with medically verified CP to either immediate MobACT or waitlist control (1:1). Participants in the waitlist control condition will receive access to MobACT only after completion of the T1 assessment, following the primary between-group comparison. A 6-month follow-up (T2) will be conducted in the intervention group only to examine maintenance of treatment effects. The primary outcome will be pain acceptance, assessed with the Chronic Pain Acceptance Questionnaire. Pain intensity and pain interference will be key clinical secondary outcomes. Additional secondary outcomes include quality of life, sleep quality, central sensitization, pain catastrophizing, psychological flexibility, self-efficacy, coping, anxiety, and depressive symptoms. Weekly assessments of sleep quality and changes in pharmacological treatment will also be collected during the active intervention period. The economic evaluation will compare the two conditions from healthcare and societal perspectives using service utilization data, productivity indicators, and EQ-5D-3L–derived quality-adjusted life years.

**Ethics and dissemination:**

Ethical approval was obtained from the Ethics Committee of Università Cattolica del Sacro Cuore, Milan (Approval No.: 146/24). Results will be disseminated through peer-reviewed publications, international conferences and stakeholder reports for patient organizations.

**Trial registration number:**

ClinicalTrials.gov Identifier: NCT07270588.

## Introduction

1

Chronic Pain (CP) is pain that persists or recurs for more than 3 months in one or more anatomical regions, and is characterized by significant emotional distress (anxiety, anger/frustration, or depressed mood) and/or functional disability (interference with daily life activities and reduced participation in social roles), which cannot be more accurately explained by other diagnoses (Nicholas et al., 2019). Pain is defined as: “Pain is an unpleasant sensory and emotional experience associated with, or resembling that associated with, actual or potential tissue damage.” (Raja et al., 2020), as reported in the International Classification of Diseases (ICD-11) (Raja et al., 2020). Conditions such as widespread chronic pain, complex regional pain syndrome, primary chronic headache, chronic visceral pain, and chronic musculoskeletal pain affect nearly 20% of the population and represent leading causes of disability worldwide (Landi et al., 2020). CP is associated with reduced quality of life (QoL), decreased work productivity, and increased use of medications and healthcare services, representing a substantial economic and social burden with significant direct and indirect costs (Allegri et al., 2015; Maraschini et al., 2025; Toccaceli et al., 2024; Sirri et al., 2020). Consequently, effective management of CP is crucial. CP is multifactorial: biological, psychological, and social factors all contribute to the pain syndrome (Barke et al., 2022). Therefore, pharmacological and surgical approaches alone are often ineffective in alleviating pain or improving physical and emotional functioning (Landi et al., 2021), highlighting the central importance of psychotherapy for this population (Gasslander et al., 2022). Emotional distress in individuals with CP has been linked to pain-related coping styles (Pasini et al., 2024; Castelnuovo et al., 2018). Feelings of depression, anxiety, anger, and fear are bidirectionally associated with the patient's pain experience (Cattivelli et al., 2018; Castelnuovo et al., 2016). According to the fear-avoidance model, these factors influence pain intensity and pain-related disability, together with processes such as pain catastrophizing (i.e., a cluster of maladaptive cognitions and emotions arising in response to pain states) and pain-related fear, through avoidance behaviors (Giusti et al., 2017). Avoidance behaviors, such as activity restriction, may lead to physical deconditioning and further reduced QoL, producing a self-perpetuating vicious cycle (O'Carroll et al., 2026; Hill, 2019; Turk and Rudy, 1992). In this context, treatments based on Acceptance and Commitment Therapy (ACT) aim to reduce the disabling influence of pain by promoting psychological flexibility (PF), defined as the ability to remain open and responsive to present-moment experiences—including pain and discomfort—while engaging in behaviors guided by personally meaningful values (Hayes et al., 2012). This flexible approach involves a willingness to experience pain-related distress in the service of valued life pursuits, fostering engagement in meaningful activities and improving overall pain management (Schütze et al., 2018). Through increased PF, individuals can modify rigid behavioral patterns of avoidance or control that often exacerbate suffering, thereby adapting more effectively to the fluctuating challenges associated with chronic pain (Kashdan and Rottenberg, 2010). Within ACT, PF is operationalized through six interrelated processes—acceptance, cognitive defusion, present-moment awareness, self-as-context, values clarification, and committed action—that together enhance adaptive functioning, resilience, and QoL in the face of persistent pain (Landi et al., 2021; Hayes et al., 2012; Pakenham et al., 2020). ACT can be delivered in brief and modular formats, making it widely applicable, feasible, well tolerated, and effective. As a transdiagnostic approach, ACT targets core processes underlying human suffering, making it potentially suitable for all CP conditions (Feliu-Soler et al., 2018; Scott et al., 2016). Evidence shows that ACT-based treatments effectively reduce pain intensity, pain interference, and emotional distress, while improving patients' QoL (Hughes et al., 2017; Veehof et al., 2016). However, access to these programs is often limited by healthcare system constraints, shortages of trained professionals, lack of service proximity, stigma associated with psychological treatment, and patients' mobility difficulties (Heapy et al., 2015; Perlini et al., 2020). To improve the accessibility and cost-effectiveness of psychological interventions, recent years have seen the development of delivery modes complementing face-to-face treatment. Among these, internet-based self-help interventions grounded in the principles of cognitive-behavioral therapy (CBT) have proven promising for the treatment of chronic pain and related disorders (Ariza-Mateos et al., 2021; Buhrman et al., 2016; Gandy et al., 2022; Macea et al., 2010; Donisi et al., 2023; Pasini et al., 2023). Internet delivery may help overcome many access barriers (De Lucia et al., 2024). Advantages of internet-based interventions (IBIs) include reducing therapist time per patient, shortening waiting lists, enabling patients to work at their own pace, eliminating the need to schedule appointments with a therapist, increasing accessibility for a greater number of people, and potentially improving cost-effectiveness (Andersson et al., 2009; Cuijpers et al., 2008; Semonella et al., 2022). IBIs for chronic pain management has been shown to reduce pain, depression, anxiety, and disability, while improving QoL (Eccleston et al., 2014). More recently, several studies have implemented IBIs based on ACT principles (Bendelin et al., 2020; Buhrman et al., 2013; Lin et al., 2017; Trompetter et al., 2015). Evidence demonstrates that Internet-based ACT Interventions can impact pain acceptance, anxiety, depression, catastrophizing, pain interference, affective distress, pain intensity, pain-related disability, and fear-avoidance, with effect sizes ranging from small to large (Vugts et al., 2018). Despite the growing body of evidence supporting the effectiveness of ACT-based internet interventions for CP patients, no internet-based programme has ever been developed or formally evaluated for the Italian population.

### Objectives

1.1

The present study aims to examine the effectiveness and cost-effectiveness of MobACT, a guided internet-based Acceptance and Commitment Therapy (ACT) intervention adapted for the Italian adult Chronic Pain (CP) population from a Swedish programme previously tested in adults with chronic pain (Buhrman et al., 2013).

Consistent with the ACT theoretical framework and with the originally registered outcome hierarchy, the primary effectiveness outcome is pain acceptance at the post-intervention assessment (T1). Pain intensity, pain interference, quality of life, sleep quality, central sensitization, pain catastrophizing, psychological flexibility, self-efficacy, coping strategies, anxiety, and depressive symptoms are included as secondary outcomes, as they represent clinically meaningful indicators of symptom burden, emotional adjustment, and daily functioning.

In addition, the study will investigate potential moderators and mediators of treatment effects to better understand for whom MobACT may be most effective and through which ACT-related processes therapeutic change may occur.

The specific study objectives are:

To examine the effectiveness of MobACT compared with a waitlist control group at the post-intervention assessment (T1) in terms of pain acceptance;To examine between-group differences at T1 in secondary clinical and psychological outcomes, including pain intensity, pain interference, quality of life, sleep quality, central sensitization, pain catastrophizing, psychological flexibility, self-efficacy, coping strategies, anxiety, and depressive symptoms;To investigate baseline and process-related variables as potential moderators and mediators of treatment effects;To evaluate the cost-effectiveness of MobACT compared with the waitlist condition at T1.

The 6-month follow-up assessment (T2) will be used to evaluate the maintenance of treatment effects within the intervention group. No between-group effectiveness or cost-effectiveness comparisons will be conducted at T2, as participants allocated to the waitlist condition will receive access to the intervention following completion of the post-intervention assessment (T1).

## Methods

2

### Study design

2.1

This study is a multicenter two-arm, parallel-group randomized controlled trial (RCT) coordinated by the Department of Psychology, Università Cattolica del Sacro Cuore, Milan, Italy, with collaborating sites at the Università degli Studi di Verona, Verona, Italy, and Alma Mater Studiorum—Università di Bologna, Bologna, Italy, and conducted in collaboration with Linköping University, Linköping, Sweden, and Uppsala University, Uppsala, Sweden.

Participants will be randomized in a 1:1 ratio to either immediate access to MobACT or to a waitlist control condition. Participants allocated to the waitlist control condition will complete the baseline (T0) and post-intervention (T1) assessments without access to MobACT and will receive access to the programme only after completion of T1, following the primary between-group comparison. Because of this delayed-intervention design, valid between-group comparisons are restricted to T1. The 6-month follow-up (T2) will be conducted in the intervention group only to evaluate maintenance of treatment effects. Informed consent will be obtained from all participants before any study-related procedures are conducted (Figure 1 presents the study flow diagram).

**Figure 1 F1:**
[figure not shown]
CONSORT flow diagram. As this manuscript describes a study protocol, participant flow is presented prospectively. Reasons for discontinuation, withdrawal or loss to follow-up will be collected at the time the event is identified. through a brief platform message, email or phone contact from a member of the research team. Reasons will be recorded using predefined categories (e.g., time constraints, technical difficulties, symptom worsening, perceived lack of usefulness, preference not to continue, adverse event, or other reason) and will be reported descriptively in the participant flow diagram whenever provided.

This study will be conducted in compliance with the Declaration of Helsinki and with all relevant national regulations governing research involving human participants. Ethical approval has been obtained from the Ethics Committee of Università Cattolica del Sacro Cuore, Milan (Approval Number: 146/24).

### Participants

2.2

Individuals will be recruited using digital and community-based dissemination strategies, including:

Collaboration with patient associations related to chronic pain (e.g., national and regional organizations), which will share study information through newsletters, websites, social media channels, and member meetings;Word-of-mouth activity using the snowballing sample technique, supported by clinicians, researchers, and community networks who will inform individuals potentially eligible for the study;Online outreach, including the circulation of digital flyers and posts through social media platforms and thematic online groups focusing on chronic pain and psychological wellbeing.

Recruitment materials will provide standardized information regarding the study objectives, intervention characteristics, eligibility criteria, and participation procedures.

Subjects will be eligible for inclusion if they provide informed consent electronically and meet the following criteria: (a) age ≥ 18 years; (b) verified medical diagnosis of chronic pain persisting for at least 3 months; (c) access to an internet-connected device; (d) adequate digital literacy and ability to use online platforms independently; and (e) fluency in Italian.

Exclusion criteria will include: (a) current participation in psychological or psychotherapeutic treatment specifically targeting chronic pain; (b) elevated suicide risk, defined as a score ≥ 1 on item 9 of the Patient Health Questionnaire-9 (PHQ-9; “Thoughts that you would be better off dead or of hurting yourself in some way”) and/or a score ≥ 1 on item 15 of the Web Screening Questionnaire (WSQ; “Have you recently thought about harming yourself or taking your own life?”); (c) self-reported cognitive or neurological impairments potentially interfering with study participation; and (d) diagnosis of severe psychiatric conditions, including psychotic disorders, bipolar disorder with unstable manic or hypomanic episodes, severe depressive disorders, or severe personality disorders significantly affecting daily functioning.

Individuals reporting suicidal ideation will be contacted by a trained therapist, provided with information about available mental health services, and advised seeking help from their general practitioner, the local Mental Health Center or emergency services.

### Sample size calculation

2.3

The required sample size was determined using G^*^Power software (version 3.1.9.7) for an F test (ANOVA: repeated measures, within-between interaction), with the following parameters: effect size f = 0.15, alpha = 0.05, power (1-beta) = 0.95, two groups, repeated measurements, correlation among repeated measures = 0.50 and no sphericity correction for the primary two-time-point contrast. The assumed effect size was deliberately conservative. Although psychological and online ACT interventions for chronic pain often produce small-to-moderate or moderate effects on pain acceptance and pain interference (Buhrman et al., 2013; Lin et al., 2017; Trompetter et al., 2015; Vugts et al., 2018; van de Graaf et al., 2021; Vlaescu et al., 2016), a smaller effect was selected to avoid overestimating treatment effects in the first formal evaluation of an Italian internet-based ACT programme for CP and in a heterogeneous, fully online recruited sample. The analysis indicated a required total sample size of *N* = 116.

To account for potential attrition, the planned sample size has been increased to 140 participants. This inflation allows approximately 17% attrition while retaining an analyzable sample close to *N* = 116. The assumption is broadly consistent with attrition observed in the Swedish guided internet-delivered ACT trial on which MobACT is based, in which 15 of 76 randomized participants (19.7%) did not provide post-treatment data (Buhrman et al., 2013). Automated reminders, weekly notifications and the availability of therapist contact through the platform are expected to support retention in the present trial.

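### N = 116 gives about 89% power, not 95%, for the two-time-point primary contrast; with the printed inputs it reproduces only for three measurements

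*Protocol article*

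**What the plan says.** The sample size calculation (protocol article, section 2.3) was done in G*Power "for an F test (ANOVA: repeated measures, within-between interaction"), with "effect size f = 0.15, alpha = 0.05, power (1-beta) = 0.95, two groups, repeated measurements". No number follows for the repeated measurements, but the same sentence ends with "correlation among repeated measures = 0.50 and no sphericity correction for the primary two-time-point contrast". The section then states: "The analysis indicated a required total sample size of" 116. The target is raised to 140 to allow about 17% attrition. In support, the section cites the Swedish trial on which MobACT is based, where "15 of 76 randomized participants (19.7%) did not provide post-treatment data".

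The study design (section 2.1) says that "valid between-group comparisons are restricted to T1" and that T2 is collected in the intervention group only. The objectives (section 1.1) and the data analysis section (2.8) say the same. The randomised comparison therefore has two time points, T0 and T1.

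**The concern.** In this G*Power procedure the number of measurements enters both the noncentrality parameter and the degrees of freedom, so it decides the answer. The text names a two-time-point contrast, yet the result matches three time points. If three was entered, the 95% belongs to a group-by-time interaction over T0, T1 and T2, which cannot be estimated without T2 data from the waitlist arm.

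The recruitment target of 140 rests directly on 116. The 95% figure would also be carried into the results paper, where it affects how a null result on pain acceptance is read: a 5% chance of missing the assumed effect is a stronger claim than an 11% chance.

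**Working it through.** **Inputs, all from section 2.3 unless noted.** f = 0.15; alpha = 0.05; target power = 0.95; k = 2 groups; correlation rho = 0.50; no sphericity correction (epsilon = 1); 1:1 allocation (section 2.1). The number of measurements m is the quantity under test.

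**Formulas (G*Power default effect-size option, within-between interaction).**

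- lambda = f² × N × m / (1 − rho)
- df1 = (k − 1)(m − 1)
- df2 = (N − k)(m − 1)
- power = probability that a noncentral F(df1, df2, lambda) exceeds the 5% critical value of the central F

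**Step 1: reproduce the stated 116.** With m = 3, lambda = 0.0225 × 3 / 0.5 × N = 0.135N.

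- N = 115: lambda = 15.525, df = 2 and 226, power 0.9484
- N = 116: lambda = 15.66, df = 2 and 228, power 0.9501

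So 116 is exactly the smallest N that reaches 0.95 with three measurements.

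**Step 2: the contrast the text names.** With m = 2, lambda = 0.0225 × 2 / 0.5 × N = 0.09N, and df1 = 1.

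| N | lambda | df2 | Power |
|---|---|---|---|
| 112 | 10.08 | 110 | 0.882 |
| 116 | 10.44 | 114 | 0.893 |
| 140 | 12.60 | 138 | 0.941 |
| 146 | 13.14 | 144 | 0.9496 |
| 147 | 13.23 | 145 | 0.951 |
| 148 | 13.32 | 146 | 0.952 |

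The requirement is 147, or 148 in equal arms. The shortfall is (148 − 116)/148 = 22%. The type II error at 116 is 1 − 0.893 = 0.107.

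**Step 3: cross-checks.** For two groups and two times, f = 0.15 means a difference in change of 4 × 0.15 = 0.60 SD. The SD of change is √(2 × (1 − 0.50)) = 1 SD. A normal-approximation two-sample calculation on change scores gives N = 146 and power 0.898 at 116. A simulation of the two-time-point test (4,000 runs, N = 116) gave 0.896.

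**Step 4: other ways to reach 116 (even N, for equal arms).**

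| Variant | Required N |
|---|---|
| m = 4, power 0.95 | 98 |
| m = 2, one-sided equivalent (alpha 0.10) | 122 |
| m = 2, power 0.90 | 120 |
| m = 2, power 0.80 | 90 |
| m = 2, SPSS effect-size option | 582 |
| m = 2, Cohen effect-size option | 580 |
| m = 2, between-factors test | 436 |

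None returns 116. At m = 2, N = 116 would need rho of about 0.605 or f of about 0.169, and neither is stated.

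**Step 5: attrition.** 140 × 0.83 = 116.2, so the inflation step agrees with its own 17%. At the cited 15/76, 140 × (1 − 15/76) = 112.4, so about 112 would be analysable, with power 0.882.

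**Step 6: baseline-adjusted T1 comparison under the same assumptions.** The residual SD is √(1 − 0.50²) = 0.866, so the standardised difference is 0.60/0.866 = 0.693. With noncentrality 0.693 × √(N/4) and N − 3 degrees of freedom:

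- N = 116: noncentrality 3.73, power 0.959
- N = 112: noncentrality 3.67, power 0.953

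**The case against.** The best case against pressing this is that little harm follows. Power of 88% to 89% is well above the usual 80%, and the outcome, design and target of 140 can all stay. That is right, and it is why the remedy is a correction of the text and not a call for more participants.

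Second, section 2.8 leaves the primary model open between mixed-effects models and repeated-measures ANOVA, and a baseline-adjusted analysis would reach 95% on the planned sample even with 112 analysed. This stands as a way out but does not rescue the present statement. Section 2.3 powers the interaction test, section 2.8 does not commit to baseline adjustment, and section 2.8 lists adjustment for baseline covariates only among the sensitivity analyses. An ordinary group-by-time model has roughly the 0.89 figure.

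Third, that three measurements were entered is an inference, and the missing numeral may have been lost when the text was extracted. Both points are fair. The finding depends on neither, because the same sentence names a two-time-point contrast and 116 does not follow from it.

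Fourth, the attrition point is minor. The article discloses the 19.7%, calls its own assumption only broadly consistent with it, and expects reminders and therapist contact to help retention. The difference is four participants and about one percentage point of power.

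**Conclusion.** The power statement is wrong as written. With the printed effect size, alpha, correlation and number of groups, and G*Power's default effect-size definition, N = 116 gives 89.3% power for the T0–T1 group-by-time test. The stated 95% needs 148 in equal arms and is not reached even with all 140 analysed (94.1%). That three measurements were used is the only explanation found that fits every other printed input, and the design rules out that test. The consequence is moderate: the primary comparison remains adequately powered, but its stated type II error is less than half the true figure.

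**What to change.** Rerun the calculation with two measurements, state that number explicitly, and choose one of two corrections:

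1. Keep the group-by-time test and report that, for f = 0.15 and correlation 0.50, 116 analysable participants give about 89% power.
2. Name a baseline-adjusted T1 comparison as the primary analysis in section 2.8 and base the power statement on it (about 96% at 116, about 95% at 112). This holds only if the primary model is fixed to match.

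Under either option, add the analysable number expected at the cited 19.7% attrition (112), with its power: about 88% under option 1.

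The cost is a rewording of section 2.3, a sentence in section 2.8 under option 2, and matching text in the registry entry or SAP if they repeat the 95%. No extra participants are needed. Holding 95% power for the interaction test itself would instead take 148/0.83, or about 179 randomised, which this correction does not require.

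### The planning effect f = 0.15, presented as conservative, is a T1 difference of 0.60 SD for the stated two-by-two interaction, and N = 116 gives about 89% power for that contrast, not 95%

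*Protocol article*

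**What the plan says.** Section 2.3 (Sample size calculation) of the protocol article describes a G*Power calculation "for an F test (ANOVA: repeated measures, within-between interaction", with "effect size f = 0.15, alpha = 0.05, power (1-beta) = 0.95". The remaining inputs are "two groups, repeated measurements, correlation among repeated measures = 0.50" and "no sphericity correction for the primary two-time-point contrast". The parameter list does not give the number of measurements, but the last phrase makes it two. The result is a required total of 116, raised to 140 to allow for about 17% attrition.

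On the size of the effect, the section says "The assumed effect size was deliberately conservative". It describes the effects of earlier psychological and online ACT trials as small-to-moderate or moderate and continues that "a smaller effect was selected to avoid overestimating treatment effects in the first formal evaluation". It does not convert f into a standardised mean difference or into CPAQ points, and it gives no figure for the effects in the cited trials.

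Sections 1.1, 2.1 and 2.8 restrict between-group comparison to T1. T2 is collected in the intervention arm only.

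**The concern.** Cohen's f has no fixed translation into a mean difference; the translation depends on the layout. In a one-way comparison of two groups f is half the standardised difference, so 0.15 would be 0.30 SD. In a two-by-two interaction f is a quarter of the difference, so the same 0.15 is twice as large. A reader who takes section 2.3 at its word will believe that the trial has 95% power for an effect below those of earlier trials. If the planning effect is in fact above a moderate one, and the power at the stated N is below 95% even there, that belief is wrong. A non-significant primary result could then be given more weight against a modest benefit than the design supports.

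**Working it through.** **Inputs.** From section 2.3: f = 0.15, two-sided alpha 0.05 (an F test with one numerator degree of freedom), power 0.95, k = 2 groups, correlation rho = 0.50, two time points, N = 116. From section 2.1: 1:1 allocation. Equal baseline means are assumed, as expected under randomisation.

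**1. Reproducing N = 116.** G*Power's default for this test uses a noncentral F with

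lambda = f² × N × m / (1 − rho), df1 = (k − 1)(m − 1), df2 = (N − k)(m − 1),

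where m is the number of measurements.

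- m = 3: lambda = 0.0225 × 116 × 3 / 0.5 = 15.66, df 2 and 228, power 0.9501. N = 116 is reproduced exactly.
- m = 2: lambda = 0.0225 × 116 × 2 / 0.5 = 10.44, df 1 and 114, power 0.893. Power is 0.950 after rounding at N = 146, and the first even N at or above 0.95 is 148.

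Other variants with m = 2 do not give 116 either: power 0.90 needs 120, a one-sided test 122, and the software's option for f defined as in Cohen 580. The published N therefore matches three measurements, although the section describes a two-time-point contrast and T2 has no control arm.

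**2. Converting f.** Take cell means, in SD units, of (0, 0) for control and (0, D) for MobACT at T0 and T1. The grand mean is D/4, the MobACT mean D/2 and the T1 mean D/2. The interaction effect in the MobACT T1 cell is D − D/2 − D/2 + D/4 = D/4, and the other three cells are ± D/4. So f = D/4 and

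D = 4 × 0.15 = 0.60 SD.

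Check: the SD of change is SD × √(2(1 − 0.50)) = 1 SD. A t test on change with D = 0.60 has noncentrality 0.60 × √(116/4) = 3.231, and 3.231² = 10.44, the lambda found above for m = 2. A simulation at N = 116 with D = 0.60 gave power 0.893.

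Under the three-measurement layout the planning effect is no smaller: f = 0.15 is 0.64 SD if the difference appears at T1 and is maintained, or appears at T1 only, and 0.73 SD (at T2) if it grows linearly to T2. The option under which f = 0.15 would mean about 0.30 SD is the one that needs 580, so it did not produce 116.

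**3. Power at rho = 0.50.** For the baseline-adjusted analysis the residual SD is √(1 − 0.50²) = √0.75 = 0.866.

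| T1 difference | Interaction, N = 116 | Baseline-adjusted, N = 116 | Interaction, N = 140 |
|---|---|---|---|
| 0.60 SD | 89% | 96% | 94% |
| 0.50 SD | 76% | 87% | 84% |
| 0.40 SD | 57% | 69% | 65% |
| 0.30 SD | 36% | 46% | 42% |

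The 140 column assumes that no one is lost.

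**The case against.** Several points on the other side are sound.

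First, the article gives no figures for the effects in the cited trials, and its Introduction describes internet ACT effects, on a list of outcomes that includes pain acceptance, as spread from small to large. A reader might infer that the trial is shown to be underpowered for the very effects it cites. The documents do not support that: whether 0.60 SD exceeds the CPAQ effects in those sources cannot be checked here, and 0.3 to 0.5 SD is an assumed range.

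Second, it is tempting to say that the authors read f = 0.15 as 0.30 SD. Section 2.3 never mentions a standardised mean difference, so that would be a guess about their reasoning.

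Third, at 0.50 SD the power is 76% or 87%. That is below 95% but not poor. Section 2.8 allows mixed models that use incomplete data, plans baseline adjustment (as a sensitivity analysis) and commits to reporting effect sizes with confidence intervals.

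Fourth, a reader might infer that a non-significant result could not exclude effects below some fixed value such as 0.5 SD. Power does not settle that; the observed interval does. At 58 per arm the standard error is √(2/58) = 0.186 SD and the 95% half-width about 1.98 × 0.186 = 0.37 SD. A null estimate of zero would exclude benefits above about 0.37 SD, while an estimate just short of significance would leave values up to about 2 × 0.37 = 0.74 SD open.

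None of this touches the conversion of f or the mismatch between N = 116 and two time points. Both follow from the article's own inputs.

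**Conclusion.** The point holds in two parts. The planning effect is 0.60 SD at T1, above a conventional moderate effect, so calling it conservative and smaller than moderate effects misdescribes it. Separately, N = 116 gives about 89% power, not 95%, for the stated two-time-point interaction; 95% would need 146 to 148 analysable participants.

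The conversion rests on equal baseline means and holds for any correlation. The power figures rest on the article's correlation of 0.50 and on 116 analysed. The comparison with earlier trials rests on 0.5 SD as an assumed benchmark for moderate. The shortfall in power is marked at 0.3 to 0.4 SD and modest at 0.5 SD. The error lies in the sample size rationale; it does not affect the endpoint, the randomisation or the planned comparison.

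**What to change.** Rewrite section 2.3 as follows.

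- State the planning effect as a T1 difference of 0.60 SD (f = 0.15 in a two-group, two-time interaction) and give it in CPAQ points, naming the SD used. The article gives no CPAQ SD, so the sponsor must supply one.
- Delete the statement that the effect is deliberately conservative and the statement that a smaller effect was chosen.
- State the number of measurements as two, and restate the power at N = 116 as about 89% for the interaction test, or about 96% if the primary analysis is baseline-adjusted at correlation 0.50.
- Report power at 0.5, 0.4 and 0.3 SD: 76%, 57% and 36% for the interaction test; 87%, 69% and 46% with baseline adjustment.
- Say that a non-significant result will be interpreted from the observed confidence interval, with no fixed exclusion threshold.

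The cost is a rewording and no added participants. The drawback is that the stated planning assumptions will look less favourable.
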